## Abstract

**Background:**

Within construction industry, physical work exposures have long been recognized as possible determinants for musculoskeletal disorders, but less attention has been given the increasing organizational and social work hazards and stress within this industry. There is to date a lack of knowledge about how to improve organizational and social working conditions and decrease stress within the construction industry.

**Methods:**

This paper outlines the design of a controlled trial to evaluate the effectiveness of a co-created organizational-level intervention with the aim to improve role clarity, quantitative demands, staffing, planning, team effectiveness, psychosocial safety climate and stress. Two regions (> 700 employees) within one large construction company in Sweden will participate as intervention and control group. Further we present the design of the process evaluation assessing fidelity, support from managers, readiness for change and contextual factors. We will utilize questionnaires, semi-structured interviews, observations and documentation as means for data collection, hence a mixed methods approach is applied.

**Discussion:**

The study is expected to contribute to the understanding of how adverse organizational and social working conditions and stress can be improved within the construction industry. By applying co-creation we wish to develop an intervention and implementation strategies that fit to the context, are in line with the needs of end-users and are supported by all management levels - all of which are highlighted features in successful workplace interventions.

**Trial registration:**

ISRCTN, ISRCTN16548039. Registered 12/02/20. Retrospectively registered

## Background

Working conditions are an important health determinant [1]. Many studies have identified the physical hazards of the construction trade and the following health effects [2]. However, there has been an intensification of work across the labor market over the past decades and psychosocial risk factors are common [3]. Also, within the construction industry has work become more stressful [4]. Hence, not only physical hazards but also the psychosocial work environment should be considered among construction workers [5]. There is, however, a dearth of knowledge on the relationship between adverse factors in the psychosocial work environment and mental health problems within male dominated industries in general [6] and in the construction industry specifically [7]. Further, the size and scope of the problem seem uncertain. Reports show that the industry has the second highest incidence rates regarding occupational mental health disorders in the Netherlands [7], while, on the other hand, in the UK, construction workers have a lower incidence of mental illness compared to workers in other industries [8]. Swedish statistics show similar figures as in the UK, however poor mental health as a cause of sick leave is increasing across the Swedish labor market, including the construction industry [9, 10]. Stress related diagnoses, such as acute stress reaction and burnout, are increasing the most [9].

A possible consequence of stress among construction workers is an increased risk of being involved in workplace accidents [11–13]. A Swedish report [11] shows that construction workers who report daily stress suffers a four times as high risk of being in a serious workplace accident compared to those reporting perceived stress seldom or never. Hence, understanding the relationship between psychosocial work conditions and stress and how these working conditions can be changed within the construction industry can lead to a decrease in both stress and workplace accidents. Further, several countries’ occupational health and safety legislation obliges employers to act against psychosocial risk factors that cause work stress [14]. In Sweden, the legislation on organizational and social work environment was sharpened in 2016 when new provisions were implemented, placing requirements on the employer regarding knowledge requirements, goals, workload, working hours and victimization.

One challenge is to identify the important psychosocial risk factors. A recent systematic meta-review [1] concludes that high job demands, low job control, role stress, bullying and low social support in the workplace are risk factors for common mental health problems. However, the root cause of psychosocial risks and work-related stress has been proposed to be the psychosocial safety climate [15] in the organization. Hence, this is also an important factor to examine.

Interventions to address work-related stress are increasing but are mainly secondary or tertiary [16, 17]. Secondary interventions are directed at individuals at risk of developing stress responses. Tertiary interventions focus on treating existing diagnosed conditions. Primary interventions on the other hand are preventive and aim to deal with organizational factors as causal stress agents. However, there is a dearth of knowledge on how to improve organizational and social working conditions and prevent poor mental health at the workplace [18]. Thus, to address this knowledge gap the focus of this project is on a primary organizational-level intervention. The present project is expected to contribute to the understanding of how adverse organizational and social working conditions can be improved.

It is argued that both effect and process evaluations are needed when evaluating complex organizational-level interventions [19–21] in order to gain a better understanding of the mechanisms of change. In the present study we will follow these recommendations. There are several theoretical frameworks deriving from different disciplines, for how to evaluate the implementation process [21–25]. In this study, the Medical Research Council (MRC) guidance on process evaluations [21] will mainly be used together with parts of the Framework for Evaluating Organizational-level Interventions by Nielsen and Randall [22]. The latter will be used as it has been developed specifically to evaluate organizational-level occupational health interventions and because using the same terminology as other researchers within the field has been recommended [26].

### The implementation process and co-creation

Conditions found to be crucial for successfully implementing change are: fit of the intervention in to the workplace context [22], integration of the intervention activities into already existing structures [27], and that the intervention build on a participatory approach for both the management and the target group for change, the so called end-users [28, 29]. Hence, it is important that the intervention is tailored for the specific group and context [30, 31]. Finally, the support from line and senior managers has been acknowledge as crucial for the implementation to succeed [22, 32, 33]. To meet these implementation conditions Leask et al. [34] recommend that researchers and different stakeholders from the organization undertaking the change should co-create the intervention. This process should for example include shared decisions on who should be included in the co-creation, problem formulation and goal setting. We will use co-creation in order to ensure relevance regarding content of the intervention and to enhance the implementation process variables described above.

### Aim and objectives

The aim of this project is to contribute to the knowledge on how to change adverse working conditions within the construction industry by evaluating a co-created intervention with the aim to improve organizational and social working conditions, enhance team-effectiveness and decrease stress.

The primary objective is to compare the effectiveness of a co-created intervention versus standard procedures on role clarity, quantitative demands, staffing, planning, team effectiveness, psychosocial safety climate and stress (effectiveness evaluation).

The secondary objective is to evaluate the implementation process regarding fidelity (adherence to the intervention) and barriers and facilitators to adherence. This will be done using mixed methods, that is, both qualitative and quantitative methods will be used to collect data.

## Methods

### Trial design

The study is a controlled trial with before and after measurements involving two regions (one intervention and one control region) and approximately 45 construction teams (projects). Randomization was not possible due to the fact that the intervention region wanted all groups (building projects) to receive the intervention. Instead we matched a control group (region). The criteria applied for matching were type of work (same branch) and region size (*N* > 300). Employees of the participating regions will be invited to complete outcome questionnaires during working hours at baseline and at 12 months follow-up. Our intention is to also include an 18-month follow-up questionnaire, however this has not yet been approved by the control region.

### Trial registration

The trial has been registered in the ISRCTN registry (16548039). Further, the study has been approved by the Swedish Ethical Review Authority (Reg. No. 2019–02662).

### Study setting and study population

The Swedish construction industry occupy around 300,000 individuals in Sweden. The gender distribution is uneven and most employees are men [11]. Approximately 15% are employed in large companies and the studied organization is one of the largest construction companies in Sweden. The company operates internationally but the focus of this project is on employees and work sites located in Sweden.

#### Recruitment of regions

Two large construction companies in Sweden were contacted and after a few meetings one of them agreed to participate in the study. A short listing of eligible branches and regions was conducted in collaboration with representatives from the company. The building construction branch was chosen as the context for the intervention. The national manager of health and safety took on the responsibility to inform the regions about the study and look for potential participants. One region (employees = 360) applied to take part in the study with one condition, the whole region should be included in the intervention. Hence, this became the intervention group. The matched control region (employees = 450) accepted to participate after discussions in their highest management team.

#### Participant eligibility criteria

Participants employed by the included regions were eligible to participate in the study. This includes both blue- and white-collar workers within the building projects but also the white-collar workers belonging to the supporting group (operational support). Employees reporting to managers outside the region, the regional manager, the districts managers, and the regional managers staff were excluded from the effectiveness evaluation since the interventions do not target their working situation. However, they are important stakeholders in relation to the implementation process and therefore included in the process evaluation.

### Intervention development and planning

The project includes three phases and follow the evidence based psychosocial risk management approach [35], which can be summarized in five steps: preparation, screening, action planning, implementation and evaluation. During preparation we formed an operative steering group consisting of the Human Resource (HR) generalist, the Health and Safety manager, the manager of development and the project leader from the research team. The regional manager was assigned as project owner together with the highest management team. In order to reach a buy in among the senior management all suggestions were presented to the highest management team who agreed to include the prioritized outcomes and intervention activities in the business case for 2020. An already existing work group, called the Health and Safety team, was chosen as the co-creation group. The group consists of representatives from different levels (e.g. first-line managers, site managers) and districts within the region, union representatives together with the HR generalist, the health and safety manager, the manager of operational support and the manager of development. Screening included a formative evaluation to assess the current working conditions. We carried out interviews (*n* = 25) and a survey in order to answer the questions: *What works well?* and *What needs to be improved*? regarding the organizational and social work environment. In order to give the intervention and the control group similar conditions, the survey was also conducted in the control group, however no feedback of the results was given to the control group.

In the second phase (action planning) researchers and the Health and Safety team co-created the outcomes, the intervention components and the implementation strategies. Hence, a co-created program logic was created, which is a recommended model [36]. We also discussed and formulated suggestions for how to design the implementation process. During the third phase the intervention will be implemented and evaluated.

#### Program logic and interventions

In the co-creation group, we produced a co-created program logic working our ways backwards in the logic model, see Fig. 1. The long-term outcomes, stress and team effectiveness, were firstly chosen, then the short-term outcomes and finally the intervention components identified in relation to the outcomes. The short-term outcomes were chosen after thorough investigation of the results from the needs assessment (interviews and survey). This was an iterative process going on for 4 months. Hence, the intervention components fit well into the context, senior management supports them, and the co-creation group (Health and Safety team) has been involved in the discussion and decision-making regarding outcomes and interventions.

**Fig. 1 Fig1:**
[figure not shown]
Program logic for the intervention. (+) = an increase in the outcome, (−) = a decrease in the outcome

#### Implementation strategies

This is an intervention study, however since research has shown the great importance of a well-planned and executed implementation process [26] we decided, not only to make a program logic for the intervention but also to include a clear description of what implementation strategies that will be used. It has been suggested that the choice of implementation strategies should be theory-based, and target identified barriers [26]. Therefore, we utilize the Com-B model [37] to address barriers and facilitators and to choose implementation strategies to target these barriers. However, some of the implementation strategies have been chosen by the research team given barriers and facilitators identified in earlier research, such as lack of fit to the context, and lack of support from managers [38]. See Table 1. To facilitate comparison between studies, we used the terminology of Powell et al. [40] to describe the implementation strategies.

**Table 1 Tab1:** Description of implementation activities, content according to Powell (implementation strategies), barriers to target and theory used

Activity	Implementation strategies included	Barriers to target	Who identified the barrier?	Theory
Co-creation	Use advisory boards and workgroups	Lack of fit into the context	Literature: [33, 38] Lack of support from managers	
		Lack of support from managers		
	Conduct local consensus discussions			
		Lack of integration in existing structures	[22, 31] Lack of fit into the context	
			[27] Lack of integration in existing structures	
Formative evaluation	Conduct local needs assessment	Lack of fit into the context	Literature: [22, 39] Lack of readiness for change	
		Lack of readiness for change among end-users		
Feedback of results and rational to interventions	Conduct educational meetings	Lack of understanding	The co-creation team	Lack of motivation COM-B model
Develop educational materials	Develop educational materials	Lack of competence	The co-creation team	Capability and opportunity COM-B model
Learning collaborative	Identify early adopters	Lack of motivation	The co-creation team	Lack of motivation COM-B model
	Shadow other experts	Lack of competence		
	Visit other sites	Lack of understanding		
	Create a learning collaborative			

#### Sample size /power calculations

Since the size of the intervention and control region was given, we performed power calculations. However, since the outcomes were chosen through co-creation later in the process we elaborated with different mean differences (5, 7, 9 and11) and different standard deviations (SD) 10, 15, 20 and 30. Based on a level of significance (α) of 0.05, results show a desired statistical power (1-β) of 0.9 given a mean difference of 5 and a SD not higher than 15. A SD of 20 with the same mean difference gives a statistical power (1-β) of 0.8. Given a higher mean difference between the intervention and control group, power increases, even with larger standard deviations. A mean difference of 9 and a SD of 30 gives a statistical power (1-β) of 0.8.

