### Statistical methods (intervention effectiveness)

To evaluate the effect of the intervention we will examine between group differences over time. The analyses will consider the clustering of observations of workers within the working team (project), as well as the repeated measurements within each worker. Intention-to-treat analyses will be used and where relevant, compared to per-protocol analyses. Adjusted models will be applied if potential confounders are unevenly distributed and if this is likely to affect the results when the two groups (intervention and control) are compared.

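### The stated powers of 0.9, 0.8 and 0.8 do not follow from the stated region sizes, and the 0.8 for a difference of 5 at SD 20 is fragile under the planned clustered analysis

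*Protocol article*

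**What the plan says.** The protocol article, under Sample size /power calculations, treats the region sizes as fixed and computes power rather than a sample size. Of the inputs it says "we elaborated with different mean differences (5, 7, 9 and11) and different standard deviations (SD) 10, 15, 20 and 30". The significance level is given ("Based on a level of significance (α) of 0.05") without saying whether the test is one- or two-sided. Three results are printed:

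- The first scenario, 5/15 for short, is reported as "a desired statistical power (1-β) of 0.9 given a mean difference of 5 and a SD not higher than 15".
- The second scenario, 5/20 for short, keeps the difference and raises the spread; its power is lower, at 0.8.
- The third scenario, 9/30 for short, is reported as "A mean difference of 9 and a SD of 30 gives a statistical power (1-β) of 0.8".

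The section prints no number analysed, ICC, design effect, response rate or loss to follow-up.

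The sizes are elsewhere. Recruitment of regions gives 360 employees in the intervention region, and for the other arm: "The matched control region (employees = 450) accepted to participate". Trial design refers to "approximately 45 construction teams (projects") and says that employees are invited to complete questionnaires at baseline and at 12 months. Statistical methods (intervention effectiveness) says: "The analyses will consider the clustering of observations of workers within the working team (project"), and adds that the repeated measurements within each worker will also be taken into account.

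**The concern.** The printed powers are presented as properties of this design, but they are not tied to a sample size or to the planned analysis. If all 810 employees respond, about 45 projects means about 18 workers per project, so even a small ICC reduces the effective sample size noticeably. Non-response at either survey reduces it further, while use of the baseline measurement increases it. None of these quantities appears beside the figures.

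What is at stake is how the result will be read. A null finding on stress would be interpreted against a stated power of 0.8 to 0.9, and the reader has no means of judging whether that power was available.

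**Working it through.** **Inputs from the article.** n = 360 and 450; about 45 projects; α = 0.05 (two-sided assumed); difference/SD pairs 5/15, 5/20 and 9/30. Results below are in that order.

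**Step 1: reproduce the stated figures from the region sizes.** For independent responders, SE = SD × √(1/450 + 1/360) = SD × 0.0707, and power = Φ(difference/SE − 1.96).

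- 5/15: SE 1.061, ratio 4.71, power 0.997 (stated 0.9)
- 5/20: SE 1.414, ratio 3.54, power 0.942 (stated 0.8)
- 9/30: SE 2.121, ratio 4.24, power 0.989 (stated 0.8)

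A one-sided test moves further away (0.999, 0.971, 0.995). Smaller sizes do not match either: 350 per arm, in line with the abstract's total of more than 700, gives 0.993, 0.911 and 0.978; 300 per arm gives 0.983, 0.865 and 0.957.

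**Step 2: which n would give the stated figures?** n per arm = 2 × SD² × (1.96 + z_power)² / difference².

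- 5/15 at 0.9: 2 × 225 × 10.51 / 25 ≈ 189
- 5/20 at 0.8: 2 × 400 × 7.85 / 25 ≈ 251
- 9/30 at 0.8: 2 × 900 × 7.85 / 81 ≈ 174

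Allowing for rounding to one decimal does not help. With the same formula, power between 0.75 and 0.85 needs about 222 to 287 per arm at 5/20 but about 154 to 199 at 9/30, and these ranges do not overlap. Read as minimum levels, the smallest size that meets all three is about 251 per arm (0.962, 0.800, 0.919). That is 502 of 810 employees, or 62%, a reduction by a factor of about 1.6.

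**Step 3: power under the planned clustering.** ICC and response are not in the article, so both are assumed. Let m = 18 × response and design effect = 1 + (m − 1) × ICC. Each arm's n is multiplied by the response and divided by the design effect. Power comes from the noncentral t distribution with 45 − 2 = 43 df, with equal cluster sizes and no baseline adjustment.

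Example, full response and ICC 0.05: design effect = 1 + 17 × 0.05 = 1.85; effective n = 450/1.85 = 243 and 360/1.85 = 195.

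| Response | ICC | 5/15 | 5/20 | 9/30 |
|---|---|---|---|---|
| 100% | 0.01 | 0.989 | 0.892 | 0.969 |
| 100% | 0.02 | 0.978 | 0.847 | 0.948 |
| 100% | 0.05 | 0.923 | 0.719 | 0.862 |
| 80% | 0.02 | 0.955 | 0.784 | 0.909 |
| 70% | 0.05 | 0.866 | 0.633 | 0.788 |
| 60% | 0.05 | 0.832 | 0.592 | 0.749 |
| 60% | 0.10 | 0.718 | 0.477 | 0.627 |

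Solving for power 0.8 at 5/20 gives a largest tolerable ICC of about 0.031 at full response, 0.016 at 80% and 0.006 at 70%. At 60% response with no clustering (270 and 216 independent responders, normal approximation as in Step 1), 5/20 has power 0.78.

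**Step 4: credit for the baseline measurement.** With an assumed baseline–follow-up correlation of 0.5, the variance is multiplied by 1 − 0.5² = 0.75. At ICC 0.05, 5/20 then has power 0.84 with full response and 0.76 with 70%.

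**The case against.** A reader might infer that the printed powers come from a calculation that ignored clustering and non-response, and that the design therefore delivers less than stated. The documents support neither step. The calculation with independent responders and full response gives 0.942 to 0.997, well above the printed values, so some reduction may already have been made without being reported. Alternatively, the values may be loose lower bounds, and the phrase about an SD not above 15 is compatible with that. The section is silent, and silence does not show that no allowance was made. Nor is a shortfall established: at ICC 0.01 or 0.02 with full response all three levels are met, and the planned use of repeated measurements would add power that a purely downward correction ignores.

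Further points can fairly be made. Every ICC, response rate and correlation used above is an assumption. The figure of 18 per project divides all employees by all projects, although the eligible population includes operational-support staff and excludes some managers and staff. An article may leave detail to a fuller protocol, and the region sizes were fixed, so the calculation set no recruitment target.

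These arguments limit the point but do not remove it. The article prints specific powers, and these do not follow from the sizes it also prints. If they are lower bounds, 0.8 stands for 0.989 at 9/30 and tells the reader little. If a reduced n was used, it is not stated, and no single n gives the three figures as exact or rounded values. This concerns figures that were published, not detail left out.

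**Conclusion.** The point holds in this form: the printed powers cannot be reproduced from the region sizes, their basis is undisclosed, and they are not linked to the analysis by project. Whether clustering or non-response was already allowed for cannot be determined from the text.

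The practical weakness lies in the 5/20 claim. The margin implied by 251 per arm would cover roughly 62% response with no clustering, or an ICC of about 0.03 with full response, but not appreciable amounts of both. Baseline adjustment with a correlation of 0.5 restores 0.8 at ICC 0.05 only if response is high. The 5/15 and 9/30 claims survive the milder assumptions and fall below their stated levels only in the harsher ones.

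These sizes rest on the assumed ICC (0.01 to 0.10), response (60% to 100%) and correlation (0.5), and on equal project sizes; unequal sizes would lower power further. The design effect covers projects only. With one region per arm, no calculation of this kind captures a region-level effect.

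**What to change.** Replace the printed powers with power for the planned clustered, paired analysis:

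- State the number analysed per arm and whether the test is two-sided.
- Use the design effect 1 + (m − 1) × ICC with about 45 clusters and the corresponding t degrees of freedom (about 43), at ICC 0.01, 0.05 and 0.10.
- State an expected paired response (baseline and 12 months) and an assumed baseline–follow-up correlation.
- Report the difference in the stress score, the primary outcome, that is detectable with 80% power under these inputs.
- If the existing figures already contain an allowance or are meant as lower bounds, say so and give the n behind them.

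The cost is recalculation and wording. The region sizes are fixed and there is no need to enlarge the trial. The downside is that the stated power may become less favourable in some scenarios.

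### Power of 0.8 is stated both for a difference of 5 with SD 20 and for a difference of 9 with SD 30; one sample size cannot give both

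*Protocol article*

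**What the plan says.** The sample size section of the protocol article explains that power was calculated because the sample could not be chosen: "Since the size of the intervention and control region was given, we performed power calculations". The outcomes were settled later, so the authors varied the mean difference (5, 7, 9 and 11) and the SD (10, 15, 20 and 30). The alpha is stated ("Based on a level of significance (α) of 0.05"); sidedness is not.

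Three results are reported:

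- Difference 5, SD up to 15: "results show a desired statistical power (1-β) of 0.9 given a mean difference of 5 and a SD not higher than 15".
- Difference 5, SD 20: "A SD of 20 with the same mean difference gives a statistical power (1-β) of 0.8".
- Difference 9, SD 30: "A mean difference of 9 and a SD of 30 gives a statistical power (1-β) of 0.8".

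The section gives no number analysed and no allowance for non-response or clustering. The section on recruitment of regions gives the head counts: "One region (employees = 360) applied to take part in the study" and "The matched control region (employees = 450) accepted to participate". The primary outcome section describes stress as three items with response categories from 1 to 5.

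**The concern.** When sample size and alpha are fixed, the power of a two-group comparison of means depends on the difference and the SD only through their ratio. The ratio is 5/20 = 0.25 in one statement and 9/30 = 0.30 in the other, yet both are given power 0.8. The larger standardised difference must have the higher power.

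These sentences are the article's only statement of what the trial can detect. If one of them is wrong and the sample size behind them is not given, a reader cannot tell whether the chance of missing the 5/20 effect is about 20% or about 35%.

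**Working it through.** **Inputs.** Alpha 0.05 and the three difference/SD/power statements come from the sample size section; the head counts of 360 and 450 come from the section on recruitment of regions. Two-sided testing and equal arms are assumptions here; alternatives are tried below.

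**Formulas** (normal approximation, n per arm, d = difference/SD):

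- n = 2(z₀.₉₇₅ + z_power)² / d²
- power = Φ(d·√(n/2) − 1.960)

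**Step 1. Sample size implied by each statement.**

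| Difference/SD | d | Stated power | n per arm needed |
|---|---|---|---|
| 5/15 | 0.333 | 0.9 | 190 |
| 5/20 | 0.250 | 0.8 | 252 |
| 9/30 | 0.300 | 0.8 | 175 |

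For equal power, the sample sizes for 5/20 and 9/30 must differ by the factor (0.30/0.25)² = 1.44, and 252/175 = 1.44. This factor does not depend on alpha or sidedness.

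**Step 2. Power for all three at each implied n.**

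| n per arm | 5/15 | 5/20 | 9/30 |
|---|---|---|---|
| 175 | 0.877 | 0.647 | 0.801 |
| 190 | 0.901 | 0.683 | 0.832 |
| 252 | 0.963 | 0.801 | 0.920 |

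Worked for n = 252: √126 = 11.225. For 5/20, 0.25 × 11.225 − 1.960 = 0.846 and Φ = 0.801. For 9/30, 0.30 × 11.225 − 1.960 = 1.407 and Φ = 0.920.

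**Step 3. Rounding.** Reading each figure as rounded to one decimal, the values of n that fit are:

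- 5/15 at 0.9: 162 to 233
- 5/20 at 0.8: 223 to 287
- 9/30 at 0.8: 155 to 199

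The 5/15 range overlaps each of the others. The 5/20 and 9/30 ranges do not overlap. Any n that brings 5/20 to 0.75 brings 9/30 to about 0.885, which rounds to 0.9. A search over 20 to 599 per arm found no n that gives 0.9/0.8/0.8 to one decimal. The closest single n, 212 per arm, gives 0.93/0.73/0.87.

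**Step 4. Other assumptions.**

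- *One-sided alpha:* 198 per arm for 5/20 and 138 for 9/30. At 198, power at 9/30 is 0.91; at 138, power at 5/20 is 0.667.
- *Allocation 360:450:* totals of 509 and 355. The powers are 0.801 and 0.920 at the first, and 0.648 and 0.802 at the second.
- *t test with 43 degrees of freedom* (about 45 teams less 2): the one-decimal ranges are 233 to 300 for 5/20 and 162 to 208 for 9/30, again with no overlap.
- *Common non-response or design effect:* this shrinks n by the same factor in every scenario, so it only moves the calculation along one scale of n.

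**Step 5. The 5/15 statement as a threshold.** It says that 0.9 is reached up to SD 15. On the SD grid used, that requires power of at least 0.9 at SD 15 and below 0.9 at SD 20. The first needs n ≥ 190. The second needs n up to about 2(1.960 + 1.282)²/0.25² ≈ 336. The 252 per arm implied by the 5/20 figure lies inside 190 to 336, so these two statements agree.

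**The case against.** The strongest defence is to read every figure as a minimum. From 252 per arm upwards, power is at least 0.96, 0.80 and 0.92, and all three statements would then be true. But the text says that the scenario gives a power of 0.8, not at least 0.8. On this reading 9/30 would also reach the 0.9 that the plan calls desired, and it would be odd to report it as 0.8. A different n for each scenario would fit too, but the section treats the size as given.

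Some stronger readings are tempting and are not supported:

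- *All three figures conflict with one another.* The 5/15 statement is worded as a threshold and is compatible with the 5/20 figure. The firm conflict is between 5/20 and 9/30.
- *The 5/20 power is the overstated one, so the trial is weaker than claimed.* The documents do not show this. With about 252 per arm, 9/30 is the wrong figure, and it is understated.
- *The head counts refute the figures.* With all 360 and 450 employees and no clustering, the powers would be 0.997, 0.942 and 0.989. But the section does not say that every employee is analysed, some staff are excluded by the eligibility criteria, and the analysis is to account for clustering. An effective sample below the head count is to be expected.
- *The differences are on a 0–100 stress score.* No section mentions such a score, and the outcomes were chosen after the power grid was set up.

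It is also fair to say that no recruitment target rests on these figures. That limits the consequence but does not make the pair of statements true.

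**Conclusion.** The point holds for the pair 5/20 and 9/30. As written, at least one of these two powers is wrong for any single effective sample size. The gap is material: about 0.92 instead of 0.8 for 9/30, or about 0.65 instead of 0.8 for 5/20, depending on which figure is kept. The conclusion rests on three things: one sample size for all scenarios, as the section implies; power that depends on the ratio of difference to SD; and 0.8 read as a value rather than a minimum. It does not rest on sidedness, allocation, response rate or a common design effect. The exact sample sizes quoted assume two-sided testing and equal arms.

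Which figure is wrong, and whether the correction makes the trial look stronger or weaker, cannot be decided from the article.

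A smaller related point is that the metric is not named. The mean of items scored 1 to 5 cannot differ by 5 or more. A sum of three such items runs from 3 to 15, so its SD cannot exceed about 6. SDs of 10 to 30 fit neither.

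**What to change.** In the sample size section:

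1. State the one effective sample size per region used in the calculation, whether the test is one- or two-sided, and any allowance for non-response and clustering.
2. Recalculate all the stated powers from that sample size, preferably as one table of differences 5, 7, 9 and 11 by SDs 10, 15, 20 and 30, and restate whichever figures change.
3. State the score metric to which the differences of 5 to 11 and the SDs of 10 to 30 refer. The sponsor has to supply this; it should not be assumed.

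The cost is a short recalculation and a wording correction. Recruitment, data collection and analysis do not change.
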